### Cardiac rehabilitation program

2.10

The CRP applied to patients who are going to be recruited for the study is composed of the following steps: initial rest, warm-up, resistance, and relaxation phase. The program is performed 3 times a week (Mondays, Wednesdays, and Fridays) totalizing 60 minutes per day, divided as follows: 5 minutes of initial rest, which aims at assessing the BP, HR, and signals and symptoms commonly found in subjects with CVD; 15 minutes of warm-up, performing overall stretching, lower limb exercises, upper limb exercises, and exercises combining both modes; 30 minutes of resistance phase, performing individualized aerobic exercise according to their HR reserve values,^[52]^ using bicycle and treadmill (15 minutes of exercise in each one of these ergometers). In both ergometers, the HR is measured at the 4th and 10th minute, and in bicycle, the BP is also measured. If the patient has some physical restriction, the protocol will be performed in only one of the ergometers (in this case, the HR and BP are measured at the 5th, 15th, and 25th minute); 10 minutes of cooling down, performing a cardiovascular deceleration, for example, with few laps around the room, and finally stay at rest. At the end of this phase, the HR is measured and, if necessary, so is the BP.

### Signals and symptoms identification

2.11

For the identification of the signals and symptoms during the CRP, a record is going to be prepared for each patient, containing the additional personal data, clinical diagnosis, use of medicines, and the signals and symptoms commonly found during CRP.

The most prevalent signals and symptoms found during CRP are symptoms: fatigue, muscle pain, angina, dizziness, nausea, and cramp; and signals: changes in pulse rate, increased systolic blood pressure during the exercise, increased diastolic blood pressure during the exercise, tachypnea, and pallor.

The signals are going to be observed and identified by previously trained professionals, and the symptoms are going to be referred to and/or confirmed by the patient at the end of the session. The observation of signals and symptoms is going to be performed during all phases of the session (initial rest, warm-up, resistance, and cooling down).

When the changes in pulse rate have been observed, the patients are going to perform the session with an electrocardiogram and the tracing is going to be recorded and analyzed to identify the rhythm disorder presented.

The evaluation of signals and symptoms is going to be performed during the 24 sessions. The symptomatology is going to be counted per session, regardless the number of times that the same signal/symptom occurs during the session.

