Taken together, these data point to some gaps in the literature. How are the risk stratification protocols effective to previse signals and symptoms during the CRP? Can clinical, physical, and biochemical parameters be used to previse signals and symptoms during the CRP? If yes, is it possible to establish a cut-off point for these parameters that can better previse the appearance of signals and symptoms in these programs? Are changes in clinical, physical, or biochemical parameters induced by CRP accompanied by changes in the appearance of signals and symptoms during the CRP?

This study was designed to answer these questions: to evaluate the risk stratification protocols efficacy to previse signals and symptoms during the CRP; to analyze the correlation between clinical, physical, and biochemical parameters, measured at rest, with the presence of signals/symptoms in CRP participants; and to evaluate whether changes in clinical, physical, or biochemical parameters, induced by CRP, will influence the appearance of signals and symptoms during these programs.

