### Eligibility criteria

2.1

Subjects of both genders, with clinical diagnosis of CVD and/or cardiovascular risk factor, able to realize all the evaluations proposed and in accordance to the study procedures are going to be included. Patients with less than 30% of attendance during the period of the protocol are going to be excluded.

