### Sample characterization

2.5

For the sample characterization, the volunteers’ medical records are going to be analyzed in order to identify information about their age, gender, clinical diagnoses, cardiovascular risk factors, and associated pathologies (musculoskeletal, neurological, pulmonary, and/or metabolic disfunction).

For the volunteers’ risk stratification according to the protocols selected in this study, their clinical history and the results of their last laboratory and complementary examinations related to the cardiovascular system are going to be extracted from their medical records.

For the clinical history, information about the number of cardiorespiratory arrests, hospital days, and complications during the hospital days or after procedures are going to be considered. For the laboratory tests, blood glucose, triglycerides, total cholesterol, high-density lipoprotein (HDL)-cholesterol, and low-density lipoprotein (LDL)-cholesterol are going to be considered. For the complementary examinations, cardiovascular examinations, such as exercise stress test, echocardiogram, Holter, catheterization, myocardial scintigraph, electrocardiogram, and coronary angiotomography are going to be considered.

We are also going to measure the height in orthostatic position with a stadiometer (Sanny, Personal Caprice, Brazil) and body mass with a digital balance (Balmak, Premium, Bk–200Fa, Brazil), in order to calculate the body mass index (BMI).^[40]^

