### Evaluation of clinical parameters

2.7

In relation to clinical parameters, we are going to evaluate some of them related to the cardiorespiratory system and autonomic modulation, such as blood pressure (BP), heart rate (HR), oxygen saturation (SatO_2_), respiratory rate (f), maximal inspiratory pressure (MIP), maximal expiratory pressure (MEP), peak expiratory flow (PEF), forced expiratory volume in 1 second (FEV1), forced vital capacity (FVC), FEV1/FVC ratio, and HRV.

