#### Autonomic modulation

2.7.3

The autonomic modulation is going to be evaluated through the HRV analysis. For this analysis, the HR will be recorded beat-to-beat in a quiet room, with temperature controlled between 21° and 24° C and air relative humidity between 40% and 60%. The data collection is going to be done individually and the patients remain at rest in an orthostatic position for 30 minutes. The patients are going to be oriented to not consuming stimulant substances of the ANS such as alcoholic drinks, coffee, tea, soda, and chocolate for 24 hours before HRV analysis.

A heart rate monitor Polar RS800CX (Polar Electro OY, V800, Finland) is going to be used for HR record, and the data recorded are going to be transferred to the computer through the Polar Flow web service (https://flow.polar.com/).

For the data analysis, we are going to use 1000 consecutive RR intervals, after a digital filtering complemented by a manual filtering, to eliminate ectopic, premature, and artifacts beats, and only series with more than 95% of heart sinus beat are going to be included in the study.

Linear indices of HRV in the time and frequency domain are going to be used for HRV analysis. In the time domain, RMSSD (root mean square to the successive differences between each heartbeat) and SDNN (standard deviation of all normal RR intervals) are going to be calculated.^[46]^ In the frequency domain, the spectral components of low frequency (LF: 0.04–0.15 Hz) and high frequency (HF: 0.15–0.40 Hz) are going to be evaluated, in milliseconds squared (ms^2^) and normalized units (nu), and also the relation between LF and HF components (LF/HF). The spectral analyses are going to be calculated using the algorithm of Fast Fourier transform.^[46]^

In addition, the HRV is going to be also calculated through the quantitative analysis of Poincaré Plot, considering the following indices: SD1 (standard deviation of distances of diagonal points), SD2 (standard deviation of the distances from points to lines), and finally the SD1/SD2 that describes the ratio between short and long variations of RR intervals.^[46]^

All the HRV indices are going to be obtained using Kubios HRV Standard software – version 3.0.0 (Kubios, Biosignal Analysis and Medical Image Group, Department of Physics, University of Kuopio, Kuopio, Finland).

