### Data analysis

2.12

The normality of data is going to be analyzed using Shapiro--Wilk test. According to the distribution, the population characteristics will be presented, as mean and standard deviation for parametric distribution and median and interquartile interval for nonparametric distribution.

The relationship between the number of signals and symptoms of the patients and the scale degree of the protocols (1, 2, and 3) is going to be analyzed using Pearson correlation. The concordance degree of each protocol with the number of signals and symptoms are going to be determined using coefficient of intraclass correlation. To determine the efficacy of the risk stratification protocols as soon as clinical, physical, and biochemical parameters to previse signals and symptoms during the CRP, analysis of sensibility and specificity using ROC curve is going to be done. The sensibility, specificity, and predictive value (positive and negative) for the occurrence of events are going to be also registered. If the values of the area on the curve are ≥0.650, it will be considered significative.

To evaluate whether the clinical, physical, and biochemical modifications have influenced in the occurrence of signals and symptoms, the sphericity of the data will be verified by Mauchly test, and if the sphericity be violated, Greenhouse--Geiser correction will be performed. The comparison between the different moments of the clinical (cardiorespiratory parameters and autonomic modulation), physical (maximum isometric endurance, MIVC, cardiorespiratory fitness and physical activity level), and biochemical (IL-6, TNF-alpha, and IL-10) are going to be realized by repeated measures analysis of variance (ANOVA) and the possible differences between the moments will be performed by Bonferroni post-hoc.

The statistical significance difference adopted is going to be fixed in 5% with 95% of confidence interval. The analysis is going to be done on SPSS 15.0 version (SPSS Inc., Chicago, IL).

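### Medicines are recorded but not used in the printed change analysis, so a drug started or stopped between the two evaluations could be read as a program-induced change

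*Protocol article*

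**What the plan says.** **Medicines.** Section 2.11 (Signals and symptoms identification) plans a record for each patient "containing the additional personal data, clinical diagnosis, use of medicines, and the signals and symptoms commonly found during CRP". This is the only mention of medicines in the article, and it does not say whether the entry is repeated in the third phase.

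**Who enters.** Section 2.1 admits "Subjects of both genders, with clinical diagnosis of CVD and/or cardiovascular risk factor, able to realize all the evaluations proposed". It neither restricts drugs nor asks that they be stable.

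**What describes the sample.** Section 2.5 takes from the medical records "information about their age, gender, clinical diagnoses, cardiovascular risk factors, and associated pathologies". Drugs are not listed.

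**What is controlled before HRV.** Section 2.7.3 asks patients to avoid "alcoholic drinks, coffee, tea, soda, and chocolate for 24 hours before HRV analysis". Prescribed drugs are not addressed.

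**What is compared.** Section 2.7 makes blood pressure, heart rate and HRV candidate parameters. Section 2.12 says that the comparisons of clinical, physical and biochemical parameters between moments "are going to be realized by repeated measures analysis of variance (ANOVA"), with a sphericity check and a Bonferroni post-hoc test. It names no covariate, stratum or restricted analysis.

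**How the change is interpreted.** The last paragraph of the Introduction treats the parameter changes as ones that the program induces, and asks whether they influence signals and symptoms. Section 2 describes a single observational cohort.

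**The concern.** A before-and-after comparison in one group counts everything that happened in the interval, whatever its cause. To attribute the change to the program, one must assume that nothing else that acts on the parameters changed systematically. In patients with cardiovascular disease or risk factors, drugs acting on heart rate or blood pressure are an obvious candidate. The plan accepts the principle for HRV, since it bars dietary stimulants of the autonomic nervous system, but it stops short of prescribed drugs.

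Such a drug can act on both sides of the third objective. It can move resting heart rate, HRV and blood pressure, and it can also move outcomes counted in section 2.11, such as pulse-rate changes, rises in exercise blood pressure, dizziness and fatigue. A started or stopped drug could then produce a parameter change together with a symptom change, which is the pattern the third objective looks for.

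**Working it through.** **Inputs from the protocol article**
- 24 observed sessions after the first evaluation, then 6 months of routine (section 2.4)
- 3 sessions per week (section 2.10)
- n = 44, SD of rMSSD 17 ms (section 2.2)

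The article gives no figure of its own on medicines. The 44 cannot be reproduced, because the rMSSD difference behind it is not stated; it is used here only as an input.

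**Step 1: interval between evaluations**
- 24 / 3 = 8 weeks; 8 × 7 / 30.44 = 1.84 months
- 1.84 + 6 = 7.84, about 7.8 months at full attendance, and longer if sessions are missed and made up

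**Step 2: shift in the mean change (assumed inputs)**

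Suppose that k of 44 patients have a drug change that moves the parameter by s, in units of the SD of change, all in the same direction, and that the program has no effect.
- Mean shift = k·s / 44
- Share changed f = k / 44; added variance v = f(1 − f)s²
- Standard error = √((1 + v) / 44). Using 1/√44 = 0.151 alone would leave out the variance that the drug changes themselves add.

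| k | s | mean shift | v | SE | shift / SE |
|---|---|---|---|---|---|
| 6 | 1.0 | 6/44 = 0.14 | 0.136 × 0.864 × 1 = 0.118 | √(1.118/44) = 0.159 | 0.86 |
| 9 | 1.5 | 13.5/44 = 0.31 | 0.205 × 0.795 × 2.25 = 0.366 | √(1.366/44) = 0.176 | 1.74 |

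**Step 3: chance of a significant change with no program effect**

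With two moments the ANOVA is equivalent to a paired t test. By normal approximation, P = Φ(r − 1.96) + Φ(−r − 1.96), where r = shift / SE.
- r = 0.86: 0.135 + 0.002 = about 14%
- r = 1.74: 0.413 + 0.000 = about 41%

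The nominal level is 5%.

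**Step 4: a wider range, in rMSSD units**

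Here 17 ms is read as the SD of change, which is an assumption, since section 2.2 does not say which SD it is.

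| share with a drug change | shift 8.5 ms: mean change, P(significant) | shift 17 ms: mean change, P(significant) |
|---|---|---|
| 10% | 0.85 ms, 6% | 1.7 ms, 10% |
| 25% | 2.1 ms, 13% | 4.25 ms, 33% |
| 50% | 4.25 ms, 36% | 8.5 ms, 84% |

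The effect runs from negligible to decisive, depending on rates that the article does not give. Starts and stops that move the parameter in opposite directions would partly cancel and shrink every entry.

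**The case against.** **It is a condensed article.** Covariates and sensitivity analyses are commonly left to a full protocol or analysis plan, which is not shown. This stands to the extent that nothing can be said beyond the printed analyses. It does not remove the point. Section 2.12 does fix the test for change, as printed that test is unadjusted, and the Introduction puts a causal reading on the result.

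**Nothing shows that drugs change.** This stands. The article does not say that any patient takes a cardioactive drug, or that treatment alters during the study. The consequence is therefore conditional, and both cases in the working need all shifts to go one way. Neither reaches 1.96 standard errors.

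**Cut-offs.** A reader might infer that one cut-off for heart rate, HRV or blood pressure across users and non-users is wrong, or that mixing them always lowers the AUC. The article does not support this. Its question is predictive, "is it possible to establish a cut-off point for these parameters that can better previse the appearance of signals and symptoms", and a pooled cut-off answers it for attendees as they present. The direction is not fixed either. Assume a within-group AUC of 0.70 and a drug shift of 0.5 to 1 SD. The pooled AUC is then:
- 0.69 to 0.68 if half of the patients are users regardless of events, still above the plan's 0.650
- 0.66 to 0.61 if 70% of event and 40% of non-event patients are users
- 0.73 to 0.75 if those two shares are reversed

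**Linked changes.** A reader might also infer that drug changes would manufacture a correlation between change in a parameter and change in symptoms. Section 2.12 plans no such correlation, and any figure for it would need a further assumption about how far the drug moves symptom counts.

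**Conclusion.** The point holds for the change analysis. As printed, a drug-related shift between the evaluations cannot be told apart from a program-related one: there is one cohort, no comparison group, an interval of about 7.8 months, no stated rule on drug stability or re-recording, and an ANOVA without covariates, set beside an attribution to the program.

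The size is unknown. On the assumed inputs (6 of 44 patients at 1 SD, 9 of 44 at 1.5 SD, all in the same direction) the mean change moves by 0.14 to 0.31 SD, or about 0.9 to 1.7 standard errors. That can raise the chance of a spurious significant change well above 5%, but it does not guarantee one. The point is a cheap improvement to the plan and does not invalidate it. It does not extend to calling the pooled cut-offs wrong.

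**What to change.** 1. State in section 2.11 that medicines are recorded at both evaluations. From that record, code cardioactive drug use (yes/no) at each evaluation and whether it changed in between.
2. In section 2.12, add a repeat of the phase comparison for heart rate, HRV, blood pressure and signals/symptoms in patients whose cardioactive drugs did not change. Report it beside the full-cohort result, with the number of patients whose drugs changed.
3. Optionally, describe the ROC results for heart rate, HRV and blood pressure by drug use, labelled exploratory. With 44 patients little more is feasible.
4. If the restricted and full results differ, word the conclusion as change over the period and do not attribute it to the program.

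This concerns recording and analysis only; no patient's treatment needs to be held or altered. The cost is one coded variable per evaluation, a second medicines entry in the third phase if none is already made (hard to recover reliably afterwards), and a smaller n with less precision in the restricted analysis.

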### Data analysis

2.12

The normality of data is going to be analyzed using Shapiro--Wilk test. According to the distribution, the population characteristics will be presented, as mean and standard deviation for parametric distribution and median and interquartile interval for nonparametric distribution.

The relationship between the number of signals and symptoms of the patients and the scale degree of the protocols (1, 2, and 3) is going to be analyzed using Pearson correlation. The concordance degree of each protocol with the number of signals and symptoms are going to be determined using coefficient of intraclass correlation. To determine the efficacy of the risk stratification protocols as soon as clinical, physical, and biochemical parameters to previse signals and symptoms during the CRP, analysis of sensibility and specificity using ROC curve is going to be done. The sensibility, specificity, and predictive value (positive and negative) for the occurrence of events are going to be also registered. If the values of the area on the curve are ≥0.650, it will be considered significative.

To evaluate whether the clinical, physical, and biochemical modifications have influenced in the occurrence of signals and symptoms, the sphericity of the data will be verified by Mauchly test, and if the sphericity be violated, Greenhouse--Geiser correction will be performed. The comparison between the different moments of the clinical (cardiorespiratory parameters and autonomic modulation), physical (maximum isometric endurance, MIVC, cardiorespiratory fitness and physical activity level), and biochemical (IL-6, TNF-alpha, and IL-10) are going to be realized by repeated measures analysis of variance (ANOVA) and the possible differences between the moments will be performed by Bonferroni post-hoc.

The statistical significance difference adopted is going to be fixed in 5% with 95% of confidence interval. The analysis is going to be done on SPSS 15.0 version (SPSS Inc., Chicago, IL).

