### Study design

2.4

This study is going to be divided in 3 phases. Initially, all the volunteers are going to have their medical records analyzed, and information about the sample characterization and medical examinations are going to be extracted. Two independent blinded and trained measurers are going to realize the risk stratification of the volunteers, using the protocols described into the literature review of Silva et al.^[39]^ Following this, clinical (cardiorespiratory parameters and autonomic modulation), physical [maximum isometric resistance (MIR), maximum isometric voluntary contraction (MIVC), cardiorespiratory fitness, and physical activity level], and biochemical [interleukin (IL)-6, TNF-alpha, and IL-10] parameters are going to be evaluated by a blinded and trained measurer and the subjects are going to be accompanied during 24 sessions of their CRP routines, to register the appearance of their signals and symptoms.

In the second phase, the volunteers are going to realize their normal CRP routines for 6 months. In the third phase, the clinical, physical, and biochemical parameters, described above, are going to be evaluated by a blinded and trained measurer and the volunteers are going to be accompanied for more 24 sessions of their CRP routines, to register the appearance of their signals and symptoms as well.

The description of the phases and the volunteers that will be included in each one of them are reported at Fig. 1.

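### The intraclass correlation planned between a 1–3 risk code and a sign/symptom count cannot be interpreted, because its value depends on the count's unit and on spread as well as on how well the protocol orders patients

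*Protocol article*

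**What the plan says.** Section 2.12 (Data analysis) names three analyses that link the risk protocols to signs and symptoms.

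- A correlation of the number of signs and symptoms with the protocol degree: "scale degree of the protocols (1, 2, and 3) is going to be analyzed using Pearson correlation".
- An agreement statistic on the same pair: "The concordance degree of each protocol with the number of signals and symptoms are going to be determined using coefficient of intraclass correlation".
- For predictive efficacy, "analysis of sensibility and specificity using ROC curve is going to be done", with predictive values and an area of at least 0.650 as the criterion.

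Section 2.11 (Signals and symptoms identification) defines the count. "The symptomatology is going to be counted per session, regardless the number of times that the same signal/symptom occurs during the session", and "The evaluation of signals and symptoms is going to be performed during the 24 sessions". It lists six symptoms ("fatigue, muscle pain, angina, dizziness, nausea, and cramp") and five signs. Section 2.6 (Cardiac risk stratification) places patients in low, moderate or high risk under each of eight protocols.

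The article gives no form for the ICC (absolute agreement or consistency, single or average measure), no threshold for it, no rescaling of the count and no expected count.

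**The concern.** An ICC asks how far two readings of the same quantity coincide. In the absolute-agreement form, any difference in mean or spread counts against agreement. In the consistency form, a difference in spread still does. A risk class and a symptom count are not two readings of one quantity, so there is no reason for their values to coincide even when the class predicts the count perfectly.

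The efficacy of the risk protocols is the first aim stated in the Introduction, and the Final considerations expect the study to help therapists choose among protocols. A low concordance printed beside a good ROC area would look like conflicting evidence about a safety tool, when it may only reflect the unit in which symptoms were counted.

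**Working it through.** **Plan's own figure.** There is none to reproduce, since the article states no ICC value or threshold.

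**Inputs from the article.** N = 44; codes 1, 2, 3; 24 sessions; 11 listed items, each counted at most once per session. The ceiling of a summed count is 11 × 24 = 264. This is a ceiling only, not an expected value.

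**Assumed inputs.** 11/18/15 patients in classes 1/2/3, and every patient in a class has the same count. The protocol then orders patients perfectly (Spearman 1.00 in every row of the table below). The article gives no count distribution, so several are tried.

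**Formulas** for two columns, code x and count y, with variances s²x and s²y, covariance s_xy and mean difference D:

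- Consistency, single measure: ICC(C,1) = 2·s_xy / (s²x + s²y)
- Absolute agreement, single measure: ICC(A,1) = 2·s_xy / (s²x + s²y + D² − 2·MSE/n), where MSE is the residual mean square of the two-way layout
- If the count is exactly linear in the code with slope c (r = 1): ICC(C,1) = 2c/(1 + c²), whatever the class split

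**Counts 4/10/20 as 24-session totals.** s²x = 0.596, s²y = 40.364, s_xy = 4.846, D = 11.909 − 2.091 = 9.818, MSE = 15.634.

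- r = 4.846/√(0.596 × 40.364) = 0.988
- ICC(C,1) = 9.691/40.960 = 0.237
- ICC(A,1) = 9.691/(40.960 + 96.397 − 0.711) = 0.071

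**The same data divided by 24 sessions.** s_xy = 0.2019, s²y = 0.0701, D = 2.091 − 0.496 = 1.595, MSE = 0.131.

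- r = 0.988, unchanged
- ICC(C,1) = 0.4038/0.6663 = 0.606
- ICC(A,1) = 0.4038/(0.666 + 2.543 − 0.006) = 0.126

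**Range over assumed counts**

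| Count in classes 1/2/3 | Pearson r | ICC(A,1) | ICC(C,1) |
|---|---|---|---|
| 1/2/3 | 1.000 | 1.000 | 1.000 |
| 0/2/4 | 1.000 | 0.801 | 0.800 |
| 2/4/6 | 1.000 | 0.325 | 0.800 |
| 4/10/20 | 0.988 | 0.071 | 0.237 |
| 10/20/30 | 1.000 | 0.029 | 0.198 |
| 4/10/20 per session | 0.988 | 0.126 | 0.606 |

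The slope formula agrees: c = 2 gives 4/5 = 0.80, and c = 10 gives 20/101 = 0.198. With other class splits (15/15/14, 10/20/14, 5/15/24), counts of 10/20/30 give ICC(A,1) of 0.035, 0.027 and 0.018. The pattern does not rest on the split chosen.

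**With random variation.** In one simulated set (15/15/14 patients, Poisson means 5/15/30), Spearman is 0.94 and Pearson 0.91 for both the total and the per-session mean. ICC(C,1) moves from 0.15 to 0.75, and ICC(A,1) from 0.05 to 0.25.

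**Spread of the classes.** Writing s_xy = r·s_x·s_y, ICC(C,1) is roughly 2r·s_x/s_y when the count is much more spread than the code. Two protocols with the same r against the same count then get different ICCs if one uses the outer classes more often.

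**The case against.** The best defence is that the ICC decides nothing. It has no threshold, the article assigns the efficacy question to the ROC analysis, and a Pearson correlation on the same pair is planned alongside. A protocol that orders patients perfectly would be recognised in both. This stands, and it limits the harm to the concordance result.

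Three stronger readings are tempting, and the article does not support them.

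- **A perfect protocol is bound to show almost no concordance.** This depends on the ICC form and the count distribution, neither of which is given. Counts of 0/2/4 give about 0.80 in both forms, and 1/2/3 gives 1.00. Even for totals of 4/10/20, the average-measure consistency ICC is 2 × 0.237/1.237 = 0.38. Values near zero arise with absolute agreement and totals in the tens, or with consistency when the count rises by about 20 or more per class (40/401 = 0.10).
- **Comparisons between protocols would reflect coding rather than validity.** All eight protocols share the same 1–3 coding and are set against the same count, so coding and unit are constant between them. What can distort the comparison is how each protocol spreads patients over the classes, and r still contributes.
- **The plan neglects agreement between the two raters.** Section 2.4 says "Two independent blinded and trained measurers are going to realize the risk stratification of the volunteers", and section 2.12 names no inter-rater statistic. A condensed article may leave that to the full protocol or analysis plan, so it is no error here.

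**Conclusion.** The ICC of protocol against count is wrong as written. No choice of ICC form cures it, because the two variables are not measurements of the same quantity in the same unit. Its value for a perfectly ordering protocol could lie anywhere from about 0.03 to 1.00 under the assumed counts, and re-expressing identical data per session moves the consistency form from 0.24 to 0.61. The result therefore cannot be read as high or low concordance, and it could appear to contradict the Pearson and ROC results.

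The figures rest on assumed counts and, for the table, an assumed 11/18/15 split. The dependence on unit and spread follows from the formulas and needs neither assumption. Severity is moderate, because one supplementary coefficient is affected and the main efficacy analysis is not.

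**What to change.** In section 2.12, delete the sentence that applies the ICC to each protocol and the number of signs and symptoms. Replace it with a rank association between risk class and the sign/symptom count or rate: Spearman's rho, Kendall's tau-b or Somers' D, with a 95% confidence interval. These measures do not change with the unit of the count or with any order-preserving relabelling of the classes.

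The cost is one sentence. No new data, visits or patients are needed, and the planned ROC analysis stays as it is.
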